### Sample size and power

Considering the primary outcomes of six-month adherence, crossover, and six-month survival in the program, a sample size of 86 was calculated based on the standard sample-size formula for the proportional-hazards regression model (34). Since the evaluation is a clinic-wide retrospective implementation evaluation, it is beneficial to include as many eligible patients as receive MOUD treatment at the clinic. Therefore, a sample size of approximately 100 based on the typical clinic census will be used as a sample size of convenience as well as for improved power.

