### Setting and population

Given the clinic’s size and an accrual time of 2 years including before and after algorithm implementation, we anticipate approximately 100 participants for this evaluation. Participants will be individuals age 18 or older with current or past experience of homelessness and a diagnosis of OUD. All participants are patients at the ICC. Demographic information will be reported. The sample for comparing adherence will be restricted to participants already enrolled in the ICC for management of OUD prior to the algorithm implementation, measuring adherence at 6 months prior to implementation and 6 months after. Survival curves will be drawn from all aggregated patients in MOUD programs at 6 months pre-implementation to implementation or dropout, and from 6-12 months post-implementation or dropout.

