### Data analysis

Baseline and demographic characteristics will be summarized with descriptive statistics such as means and standard deviations for continuous variables such as age and percentages for categorical variables such as race.

To accommodate the need for OUD treatment centers to have fair and ethical treatment of patients at the clinic-wide level, we will use patients as their own controls and assess six-month adherence before and after program implementation. The evaluation will follow the same patients, either adherent or non-adherent at six months before algorithm implementation, by chart review to see if they crossed over to the opposite outcome six months after implementation. We will present adherence at endpoints six months prior to and six months after MOUD 2.0 implementation as proportions. We will qualitatively compare the proportion of adherence six months prior, i.e. adherence in 2022, to the proportion six months after. Then, a chi-squared test will compare discordant pairs, i.e. patients who became newly adherent after MOUD 2.0 and patients who became newly non-adherent.

Because we are treating adherence as a binary outcome, we will use McNemar’s test to determine differences in adherence before and after implementation, with each individual patient before and after implementation as a paired sample. The Chi-squared test statistic for McNemar’s test takes the form:

$$\chi^{2}=\frac{{\left(b-c\right)}^{2}}{b+c}$$

where χ^2^ follows the chi-squared distribution with 1 degree of freedom, *b* represents the patients who were adherent before and were not adherent after, and *c* represents the patients who were not adherent before and were adherent after.

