Finally, we will present unadjusted six-month survival curves for retention before and after implementation. While comparing unadjusted survival curves before and after MOUD program implementation has potential for survival bias (i.e., individuals need to “survive” to program implementation in order to be considered for post-implementation calculations), this comparison is given to provide a general sense of how MOUD 2.0 might affect the clinic overall and not to predict explicit dropout rates. If there is a significant number of patients not retained, descriptive statistics for this group will be reported to characterize factors associated with dropout. Secondary outcomes such as receipt of LAIB and use of opioids and of other substances during the evaluation periods will be analyzed with linear regression models for descriptive purposes. These primary and secondary outcomes may also be used for a future stepped wedge analysis in other clinics that could use the algorithm prospectively.

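### The sample size of 86 comes from a proportional-hazards formula, which does not apply to the paired McNemar test, the only formal test stated for a primary outcome

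*Protocol article*

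**What the plan says.** Sample size and power opens with "Considering the primary outcomes of six-month adherence, crossover, and six-month survival in the program" and then states that "a sample size of 86 was calculated based on the standard sample-size formula for the proportional-hazards regression model". It goes on to say that "a sample size of approximately 100 based on the typical clinic census will be used as a sample size of convenience", adding that this also improves power.

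The analyses are described under Data analysis:

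- **Adherence and crossover:** McNemar's chi-squared test on the discordant patients, "with each individual patient before and after implementation as a paired sample".
- **Retention:** "we will present unadjusted six-month survival curves for retention before and after implementation". The text says the comparison is there to give a general sense of the effect on the clinic.
- **Secondary outcomes:** linear regression, for description.

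The article names no proportional-hazards model, log-rank test or hazard ratio.

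Setting and population says of the total: "an accrual time of 2 years including before and after algorithm implementation, we anticipate approximately 100 participants". For the adherence analysis it says: "The sample for comparing adherence will be restricted to participants already enrolled in the ICC" before the algorithm was introduced.

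**The concern.** One calculation is offered for three outcomes, and its formula belongs to a kind of analysis that the article does not describe. For two of the three outcomes, adherence and crossover, it cannot apply. A proportional-hazards formula converts a hazard ratio between groups into a number of events. McNemar's test compares two counts of discordant patients within one set of pairs.

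The population does not match either. The total of about 100 includes people who join after implementation, but the paired test excludes them. The article gives no separate number for the set that is tested.

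Interpretation is what is at stake. If McNemar's test is not significant, a reader will set that result against 86 or 100 and take the evaluation to have been adequately sized. Nothing in the article supports that for adherence. The Discussion also offers the evaluation as a template for others, so the reasoning may be copied.

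**Working it through.** **1. Can 86 be reproduced?** The article gives no alpha, power, hazard ratio or event proportion, so every input here is an assumption. With equal groups, events = 4(z_α + z_β)² / (ln HR)².

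- HR 0.50, two-sided 5%, 90% power: 4(1.960 + 1.282)² / 0.4805 = 87.5, so 88 events.
- HR 0.55, two-sided 5%, 80% power: 4(1.960 + 0.842)² / 0.3574 = 87.8, so 88 events.
- Freedman's version, HR 0.55, one-sided 5%, 85% power: 86 events.
- Read as patients rather than events: HR 0.50 at two-sided 5% and 80% power needs 66 events, so 86 patients would imply that 66/86 = 77% have the event.

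Solved the other way, HR = exp(−2(z_α + z_β)/√86), so 86 events detect a hazard ratio of 0.547 at 80% power or 0.497 at 90%. Several input sets land on or near 86. The figure is therefore plausible for some survival comparison, but it cannot be confirmed or shown wrong.

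**2. What does the planned test need?** For McNemar's test with discordant proportion D and net change d, pairs = (z_α√D + z_β√(D − d²))² / d².

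Example with D = 0.30 and d = 0.163: (1.960 × 0.5477 + 0.842 × 0.5229)² / 0.02657 = (1.0735 + 0.4401)² / 0.02657 = 86.2 pairs.

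Solving for d at two-sided 5% and 80% power gives the detectable net change in percentage points. The pair counts and discordance are assumptions.

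| Pairs | D = 20% | D = 30% | D = 40% |
|---|---|---|---|
| 86 | 13.3 | 16.3 | 18.8 |
| 60 | 15.9 | 19.4 | 22.4 |
| 50 | 17.3 | 21.2 | 24.5 |

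In the other direction, a 15-point change needs 68, 103 or 138 pairs at 20, 30 or 40% discordance. At 30% discordance, the power of the uncorrected statistic for a 15-point change is 81% with 100 pairs, 76% with 86, 59% with 60 and 50% with 50.

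**3. Stated justification against stated analysis**

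| Outcome | Stated basis for size | Stated analysis | Match |
|---|---|---|---|
| Adherence | Proportional-hazards formula | McNemar, pre-enrolled patients | No |
| Crossover | Same | Discordant pairs in the same test | No |
| Retention | Same | Unadjusted curves, general sense only | Loose: same kind of outcome, no test named |

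**The case against.** The strongest reply has four parts.

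**Retention is a primary outcome, and a survival formula suits it.** This stands in part. A reader might infer that 86 supports nothing in the plan, but that goes too far. Time in the programme is a primary measure, and the article does compare survival curves. A condensed article may also leave the accompanying test, hazard ratio and power to the full protocol, so their absence is not counted here. What remains is that the article extends the same number to adherence and crossover.

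**The sample is openly one of convenience.** This also stands. The evaluation is a retrospective chart review of all eligible patients, 86 sets no recruitment target, and no patient or estimate depends on it. That lowers the severity. It does not remove the mismatch, because the same section presents about 100 as better powered than 86.

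**The power remark is not tied to McNemar's test.** Correct: it follows a list that includes retention, whose curves draw on all patients. But the list also includes adherence and crossover, so the remark covers them as written.

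**The paired set may be large enough.** It may. A reader might infer that it falls below 86, but the article gives no size. Only the restriction is certain, and 50 and 60 pairs are illustrations.

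Two further inferences are not supported. One is to shrink the 100 in proportion to the chart-review dates: the article also rests that figure on the typical census of a clinic with a steady population, which does not scale with calendar time. The other is to turn 86 patients into a small count of dropouts: no dropout rate is given, and patients present in both periods can contribute to both curves.

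**Conclusion.** The point holds as a mismatch between justification and analysis, and it should be fixed. The number 86 is not shown to be miscalculated. It is offered for adherence and crossover, where its formula does not apply, and the only formal test stated for a primary outcome runs on a restricted set whose size the article does not give.

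At 80% power and two-sided 5%, with 20 to 40% of pairs discordant, even 86 pairs would detect only net changes of 13.3 to 18.8 points; with 50 pairs the range is 17.3 to 24.5. These figures rest on assumed discordance and pair counts, so no single corrected sample size can be derived from the article.

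**What to change.** Rewrite Sample size and power as follows.

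1. Describe the sample as the clinic census, taken for convenience.
2. Remove 86 as support for adherence and crossover.
3. State the expected number of patients enrolled before implementation who can form a pair. Give the McNemar detectable change at 80% power for that number over a stated discordance range, for example 20 to 40%.
4. If 86 is kept, limit it to retention, and say whether it counts events or patients and which comparison it supports. If retention stays descriptive, dropping 86 is simpler.
5. Do not claim better power at about 100 for the paired test unless that many pairs are expected.

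The cost is a short rewrite, with no extra patients, data or analyses. The drawback is that the stated sensitivity for adherence will look less favourable than the current wording suggests.

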### Evaluation status

The MOUD 2.0 clinical algorithm was developed during the COVID-19 pandemic and implemented in the ICC in January 2023. The protocol for a retrospective implementation evaluation of the algorithm was given notice of IRB exemption in February 2023. As the evaluation involves retrospective chart review, no patients were actively recruited during this time period, but new patients continue to enroll or elect to discontinue treatment, and follow up of patients for this evaluation will be completed in early 2025. This manuscript was based on protocol version 3.

## Discussion

This is the first clinical algorithm we are aware of that incorporates long-acting injectable buprenorphine in treatment of opioid use disorder. LAIB adds an additional layer to a clinic’s strategy for improving communication and adherence between clinicians and patients. For primary care settings where monitored treatments are unfeasible, LAIB provides assurance that treatment is being delivered to its intended recipients while reducing the number of visits and improving rapport between staff and patients. Primary care settings may lack guidance on incorporating a new administration route such as LAIB. Thus, this algorithm positions LAIB among early treatment options as well as part of a stepwise progression.

Furthermore, this algorithm builds on strengths of previously published algorithms (17, 35) and offers a way to assess their effectiveness indirectly. Previous algorithms were not evaluated for their effects on patient populations using statistical methods. Therefore, there are limited data on the effects of introducing more standardized treatment options for OUD in primary care. This evaluation will add to MOUD options in primary care while serving as a template for evaluating new and existing protocols. This and future studies could also provide settings for validating screening tools for measurement-based care, by combining these screens with toxicology results.

Because of the high morbidity and mortality of OUD and the marginalized patient population, designing an ethical observational study or clinical trial can be difficult, which could possibly have limited previously published algorithms from being evaluated. This evaluation addresses such concerns by controlling by chronology and including all eligible patients in clinic-wide implementation of the algorithm. Including all patients not only promotes ethical treatment to produce satisfactory outcomes, but also removes a barrier to treatment that new treatment strategies may introduce: A new intervention such as LAIB can lead to some patients perceiving unfairness if other patients receive the intervention first, or they may feel they are being singled out for more intrusive followup if offered the treatment before others. Situating LAIB in a clinic-wide pathway promotes transparency with patients and should reduce the attrition that can be associated with introducing a new treatment strategy.

A limitation of this evaluation includes the necessity of assigning categories in the algorithm and evaluation, at the expense of nuance. The algorithm sorts patients into full, partial, and no response groups, but the ways patients benefit from MOUD can be subtle and vary from day to day. For example, a patient may benefit from buprenorphine one week and then experience a social stressor the next week resulting in diversion of buprenorphine and return to use. The narratives of such experiences are important, yet the clinical team must balance fairness with attentiveness to individual needs, as the algorithm categories demonstrate. For the sake of statistical analysis, the evaluation protocol cannot fully account for these variations when assigning binary outcomes. There are also inherent limitations to observational studies such as vulnerability to confounding, as this is not a blinded randomized clinical trial. These concerns can be mitigated by replicating the evaluation across multiple different primary care settings. As noted, after an initial implementation evaluation, a stepped wedge randomized clinical trial design could be used in similar clinics. The goals of this initial evaluation are different from those of a clinical trial, as the questions are whether the algorithm is feasible to implement and whether it benefits the MOUD clinical setting overall, not whether each individual administration of a medication has the desired outcome. Complete elimination of confounders is thus not necessary or desirable in this evaluation.

A final strength of this evaluation is the design of the algorithm in consultation with many representatives of the community, including patients (36). This algorithm was unique as it originated not only from the medical team but also through meetings with clinic management staff, leadership, and focus groups with patients. The algorithm’s development was consistent with a principle of transparency that the algorithm was intended to honor. In making this algorithm and its evaluation protocol available, greater transparency becomes available for assessing whether MOUD strategies based on this principle are effective in other primary care settings.

## Conclusion

Clinicians need the best available tools for treating OUD in primary care settings, where OUD is most likely to be encountered but also where clinical decision support is still developing. This primary care clinical support algorithm is unique in including injectable buprenorphine and urine toxicology for treating OUD. The algorithm draws from previous algorithms and feedback from clinic staff and patients to promote fairness and transparency. The goal of implementing the algorithm was to improve adherence and retention, thereby expanding access to quality care. In keeping with this principle of transparency for MOUD 2.0, we have included an algorithm evaluation protocol to be implemented in a primary care setting with a high volume of OUD and which may be replicated in similar settings.
